### **DATA HANDLING**

An Electronic Case Report Form (eCRF), designed to record all of the required information from the protocol to be reported to the sponsor on each trial participant, will be implemented in this trial. The eCRF Design task includes adapting technology and processes that manage clinical data to produce a high quality, clean and analyzable database. A correct design of an eCRF will impact in the process of collecting, entering,

---

 CPMP/ICH/363/96. ICH E9 Statistical Principles for Clinical Trials. URL: [http://www.ema.europa.eu/ema/index.jsp?curl=pages/regulation/general/general\\_content\\_001228.jsp&mid=WC0b01ac05807d91a4](http://www.ema.europa.eu/ema/index.jsp?curl=pages/regulation/general/general_content_001228.jsp&mid=WC0b01ac05807d91a4), last access: 30-Oct-2017.

 CPMP/EWP/908/99. Points to Consider on Multiplicity issues in Clinical Trials. URL: [http://www.ema.europa.eu/ema/index.jsp?curl=pages/regulation/general/general\\_content\\_001220.jsp&mid=WC0b01ac05807d91a4](http://www.ema.europa.eu/ema/index.jsp?curl=pages/regulation/general/general_content_001220.jsp&mid=WC0b01ac05807d91a4), last access: 30-Oct-2017.

 CPMP/EWP/1776/99 Rev1. Guideline on Missing Data in confirmatory trials. URL: [http://www.ema.europa.eu/ema/index.jsp?curl=pages/regulation/general/general\\_content\\_001221.jsp&mid=WC0b01ac05807d91a4](http://www.ema.europa.eu/ema/index.jsp?curl=pages/regulation/general/general_content_001221.jsp&mid=WC0b01ac05807d91a4), last access: 30-Oct-2017.

cleaning, and reporting on data recorded during clinical trials. The eCRF design includes:

- Input into the design of protocols, which define what data are to be collected and at what times.
- Design and approval of case report forms, on which participants' data are collected.
- Database design for the study, ensuring it meets requirements for data entry and reporting.

Data generated and/or collected will be registered in participating centres using an electronic data management system with remote data entry. Completeness and plausibility checks will ensure the collection of high quality data. Data management services, in addition to the necessary hard - and software, will be provided by the Data Management and Biostatistics Program of the Spanish Clinical Research Network (SCReN). An electronic Case Report Form (eCRF) will be designed, validated and implemented with MACROTM (Elsevier B.V.) and will provide electronic data capture functionality (EDC) to the investigators. The system complies with the relevant international standards and provides the capability to perform all major data management activities within a consistent, auditable and integrated electronic environment (query management, data entry, data validation, report generation). MACROTM has been designed to support compliance with the requirements of relevant Competent Authorities of Europe and the rest of the world, including the internationally recognized ICH Good Clinical Practice and FDA 21 CFR Part 11. Any data transfer will be done using secure SSL connection with encryption. Export for archiving of the clinical database including audit trails in hard- and software independent storage

formats will be provided by the Medical Statistics core facility of IDIBAPS-Hospital Clínic.

Additional services will include submission protocols, user manuals and online control for configuration and incidences.

***Palindromic Rheumatism criteria of Guerne & Weisman (1992) (18)***

- f.* Six-month history of brief-sudden-onset and recurrent episodes of monoarthritis or, rarely, polyarthritis or of soft tissue inflammation
- f.* Direct observation of one attack by a physician
- f.* Three or more joints involved in different attacks
- f.* Absence of erosions on radiographs
- f.* Exclusion of other arthritides

We use modified Palindromic Rheumatism criteria of Guerne and Weissman for this study:

- Disease evolution less than 6 month is permitted (but not less than 3 months).
- All patients included should be seropositive for RF and/or ACPA.

## **10. ADVERSE EVENT REPORTING**

A *Serious Adverse Event (SAE)* is any untoward medical occurrence that at any dose:

- results in death
- is life-threatening (defined as an event in which the participant was at risk of death at the time of the event; it does not refer to an event which hypothetically might have caused death if it were more severe)
- requires inpatient hospitalization or causes prolongation of existing hospitalization (see **NOTE** below)
- results in persistent or significant disability/incapacity
- is a congenital anomaly/birth defect
- is an important medical event (defined as a medical event(s) that may not be immediately life-threatening or result in death or hospitalization but, based upon appropriate medical and scientific judgment, may jeopardize the subject or may require intervention [eg, medical, surgical] to prevent one of the other serious outcomes listed in the definition above.) Examples of such events include, but are not limited to, intensive treatment in an emergency room or at home for allergic bronchospasm; blood dyscrasias or convulsions that do not result in hospitalization.)
- Suspected transmission of an infectious agent (eg, pathogenic or nonpathogenic) via the study drug is an SAE.

Although pregnancy, overdose, potential drug-induced liver injury (DILI), and cancer are not always serious by regulatory definition, these events must be handled as SAEs.

Any component of a study endpoint that is considered related to study therapy should be reported as an SAE (eg, death is an endpoint, if death occurred due to anaphylaxis, anaphylaxis must be reported).

**NOTE:** (PI determines if this information regarding hospitalizations are considered SAEs and should be included in the protocol. This is supplemental information that is included in BMS-sponsored trials)

The following hospitalizations are not considered SAEs in BMS clinical studies:

- a visit to the emergency room or other hospital department < 24 hours, that does not result in admission (unless considered an important medical or life-threatening event)
- elective surgery, planned prior to signing consent
- admissions as per protocol for a planned medical/surgical procedure
- routine health assessment requiring admission for baseline/trending of health status (eg, routine colonoscopy)
- Medical/surgical admission other than to remedy ill health and planned prior to entry into the study. Appropriate documentation is required in these cases.
- Admission encountered for another life circumstance that carries no bearing on health status and requires no medical/surgical intervention (eg, lack of housing, economic inadequacy, caregiver respite, family circumstances, administrative reason).
- Admission for administration of anticancer therapy in the absence of any other SAEs (applies to oncology protocols)

**The researcher must send the completed SAEs of the study immediately and within 24 hours of the site becoming aware of the event. by mail in the name of the study monitor or by fax to [name].**

## **ADVERSE EVENTS**

An Adverse Event (AE) is defined as any new untoward medical occurrence or worsening of a preexisting medical condition in a clinical investigation participant administered study drug and that does not necessarily have a causal relationship with this treatment. An AE can therefore be any unfavorable and unintended sign (such as an abnormal laboratory finding), symptom, or disease temporally associated with the use of investigational product, whether or not considered related to the investigational product. The causal relationship to study drug is determined by a physician and should be used to assess all adverse events (AE). The casual relationship can be one of the following:

Related: There is a reasonable causal relationship between study drug administration and the AE.

Not related: There is not a reasonable causal relationship between study drug administration and the AE.

The term "reasonable causal relationship" means there is evidence to suggest a causal relationship.

Adverse events can be spontaneously reported or elicited during open-ended questioning, examination, or evaluation of a subject. (In order to prevent reporting bias, subjects should not be questioned regarding the specific occurrence of one or more AEs.)

#### **NONSERIOUS ADVERSE EVENT**

- Non-serious Adverse Events (AE) are to be provided to BMS in aggregate via interim or final study reports as specified in the agreement or, if a regulatory requirement [eg, IND US trial] as part of an annual reporting requirement.
- Non-serious AE information should also be collected from the start of a placebo lead-in period or other observational period intended to establish a baseline status for the subjects.

A ***non-serious adverse event*** is an AE not classified as serious.

### **Non-serious Adverse Event Collection and Reporting**

The collection of non-serious AE information should begin at initiation of study drug.

All non-serious adverse events (not only those deemed to be treatment-related) should be collected continuously during the treatment period and for a minimum of 30 days following the last dose of study treatment.

Non-serious AEs should be followed to resolution or stabilization, or reported as SAEs if they become serious. Follow-up is also required for non-serious AEs that cause interruption or discontinuation of study drug and for those present at the end of study treatment as appropriate.

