### 6.3 TRIAL DESIGN:

This is a multi-centre , Phase IV ,open –label randomized controlled clinical trial comparing the efficacy of abatacept versus hydroxychloroquine on clinical symptoms and progression to RA in FR+ and/or ACPA+ PR patients.

Patients will be recruited in different hospitals in Spain.(multicentre) .Patients who meet the inclusion/exclusion criteria will be randomized assigned to one of the two arms

- Arm 1: abatacept monotherapy (subcutaneous route). In the first year (0-12 months) at a dose of 125 mg per week (full dose) and in the second year (12-24 months) at a dose of 125 mg every other week (q2w) (optimized dose)
- Arm 2: oral hydroxychloroquine (5 mg/Kg/day) monotherapy for 2 years (0-48 months)

Study duration: 65 months

.

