**8.8 STUDY VISIT SCHEDULE**

| Visit number                 | 1 | 2 | 3 | 4 | 5 | 6  | 7  | 8  | 9  | 10 | Treatment cessation/early withdrawal |
|------------------------------|---|---|---|---|---|----|----|----|----|----|--------------------------------------|
| Timeline (months)            |   | 0 | 3 | 6 | 9 | 12 | 15 | 18 | 21 | 24 |                                      |
| Informed Consent             | x |   |   |   |   |    |    |    |    |    |                                      |
| Inclusion/Exclusion criteria | x |   |   |   |   |    |    |    |    |    |                                      |
| Demographics                 | x |   |   |   |   |    |    |    |    |    |                                      |
| Medical history              | x |   |   |   |   |    |    |    |    |    |                                      |
| Concomitant drugs            | x | x | x | x | x | x  | x  | x  | x  | x  | x                                    |
| Clinical exam                | x | x | x | x | x | x  | x  | x  | x  | x  | x                                    |
| Joint assessment             | x | x | x | x | x | x  | x  | x  | x  | x  | x                                    |
| Routine blood test           | x |   |   | x |   | x  |    | x  |    | x  | x                                    |
| Hand/feet X-ray*             | x |   |   |   |   |    |    |    |    |    |                                      |
| Randomisation                |   | x |   |   |   |    |    |    |    |    |                                      |
| ACR/EULAR criteria for RA    | x | x | x | x | x | x  | x  | x  | x  | x  | x                                    |
|                              |   |   |   |   |   |    |    |    |    |    |                                      |
| Specific blood tests**       |   | x | x |   |   | x  |    |    |    | x  | x                                    |
| Adverse events               |   | x | x | x | x | x  | x  | x  | x  | x  | x                                    |

RF: rheumatoid factor CCP: cyclic citrullinated peptide.

Routine blood test include at least CRP, ESR Hb, WBC, platelets, cholesterol, ALT/AST creatinine

\*: unless an X-ray was performed < 6 months

\*\* : specific blood test include the determination of serum ACPA and anti-CarP autoantibodies

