**All** patients included after the screening will be followed until month 24. Visits will be performed every three months according to standard clinical practice. In each visits the achievement of the RA classification criteria will be analysed. The

frequency, duration and intensity (in a visual analogue scale) of the joint attacks will be analysed together with the presence of joint swelling or erythema.

Concomitant therapy will be recorded . Systemic steroids (oral or parenteral) in an equivalent dose higher than 7.5 mg/day of prednisone are not permitted during the study.

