## **8.9 END OF STUDY TRIAL DEFINITION**

The end of the study trial will be triggered 6 months after the last recruited patient completed final study visit (Last Patient Last Visit LPLV). This additional months will allow to monitoring and statistical analysis .

Those patients who achieve the classification criteria of RA at any time during the 24 month of the trial are considered non responders and will discontinued the study protocol and treated according to physician criteria.

Whenever possible, patients will be followed by entering their data in the CRd until the end of 10 visits

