**Serious Adverse Event Collecting and Reporting**

- All Serious Adverse Events (SAEs) that occur following the subject's written consent to participate in the study through 30\* days of discontinuation of dosing must be reported to BMS Worldwide Safety, whether related or not related to study drug. If applicable, SAEs must be collected that relate to any later protocol-specified procedure (eg, a follow-up skin biopsy).
- Following the subject's written consent to participate in the study, all SAEs, whether related or not related to study drug, are collected, including those thought to be associated with protocol-specified procedures. The investigator should report any SAE occurring after these aforementioned time periods, which is believed to be related to study drug or protocol-specified procedure.
- An SAE report should be completed for any event where doubt exists regarding its seriousness;
- If the investigator believes that an SAE is not related to study drug, but is potentially related to the conditions of the study (such as withdrawal of previous

therapy or a complication of a study procedure), the relationship should be specified in the narrative section of the SAE Report Form.

- If the BMS safety address is not included in the protocol document (eg, multicenter studies where events are reported centrally), the procedure for safety reporting must be reviewed/approved by the BMS Protocol Manager.

Procedures for such reporting must be reviewed and approved by BMS prior to study activation.

- The BMS SAE form should be used to report SAEs. If the BMS form cannot be used, another acceptable form (ie, CIOMS or Medwatch) must be reviewed and approved by BMS. The BMS protocol ID number must be included on whatever form is submitted by the Sponsor/Investigator. The CIOMS form is available at: <http://www.cioms.ch/index.php/cioms-form-i>.

- [[name]](mailto:[name])

- In accordance with local regulations, BMS will notify investigators of all reported SAEs that are suspected (related to the investigational product) and unexpected (ie, not previously described in the IB). An event meeting these criteria is termed a Suspected, Unexpected Serious Adverse Reaction (SUSAR).

Investigator notification of these events will be in the form of a SUSAR Report.

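### The protocol requires adverse event collection for 30 days after the last dose, but schedules no patient contact after month 24, when abatacept dosing ends

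*Protocol*

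**What the plan says.** **The collection window.** Protocol section 10 (Non-serious Adverse Event Collection and Reporting) requires that all non-serious events "should be collected continuously during the treatment period and for a minimum of 30 days following the last dose of study treatment". Under Serious Adverse Event Collecting and Reporting, the period for serious events runs from consent through 30 "days of discontinuation of dosing must be reported to BMS Worldwide Safety, whether related or not related to study drug".

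**Dosing.** Sections 5.2 and 6.3 give abatacept weekly in year 1 and "in the second year (12-24 months) at a dose of 125 mg every other week (q2w) (optimized dose"). The control arm is described as "oral hydroxychloroquine (5 mg/Kg/day) monotherapy for 2 years (0-48 months").

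**Contacts.** Under the visit schedule in section 8.8, all "patients included after the screening will be followed until month 24", with visits every three months. Visit 10, at month 24, is the last numbered visit and has the adverse event row ticked. The only other column, "Treatment cessation/early withdrawal", also has that row ticked but has no timing relative to the last dose.

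**After month 24 or an early stop.** Section 8.9 places the end of the study six months after the last patient's last visit, to allow for monitoring work and the analysis. It describes no patient contact in that time. Patients who meet RA criteria leave protocol treatment, and for follow-up the section says: "Whenever possible, patients will be followed by entering their data in the CRd until the end of 10 visits".

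**The concern.** Section 10 sets a collection period and section 8 sets the contacts that must serve it. For a patient who completes treatment, the contacts stop at about the moment the post-dose period starts. A statistical analysis plan cannot repair this, because it cannot schedule a contact.

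Adverse events are a named secondary outcome (section 6.2.2) and the trial is open-label. If late events are picked up only when a patient volunteers them, they may be under-recorded. Patients who stop early because they have progressed may still be seen at later three-monthly visits, whereas completers are not. Progression is the primary outcome and is planned to differ strongly between arms, so the chance of being asked about post-dose events could differ by arm as well.

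**Working it through.** **Step 1: the timelines side by side (treatment completers).**

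| Item | Abatacept | Hydroxychloroquine |
|---|---|---|
| Dosing ends (5.2, 6.3) | month 24 | 2 years in words, month 48 in brackets |
| Last scheduled contact (8.8) | month 24 | month 24 |
| Required collection ends (10) | last dose + 30 days | last dose + 30 days |

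**Step 2: days without a scheduled contact, abatacept completers.** Year-2 injections are every other week, so the last one falls between 0 and about 14 days before visit 10.

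- Last injection at the visit: 30 − 0 = 30 days uncovered.
- Last injection a full interval earlier: 30 − 14 = 16 days uncovered.

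So about 16 to 30 of the 30 days have no scheduled contact. For hydroxychloroquine the start of the window cannot be placed until the two stated durations are reconciled.

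**Step 3: weight of the window.** With 24 months taken as 730.5 days, 30 / (730.5 + 30) = 3.9%, or about 4% of a completer's adverse event period.

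**Step 4: the planning rates.** Section 9 (Sample size calculation) gives 42% control, 11% abatacept, 35 per group, Fisher's exact test, two-sided alpha 0.05 and 80% power. Full enumeration of Fisher's test at 35 per group gives 79.6% power (81.1% at 36), so the plan's figure is reproduced to rounding. The present point reuses only the two rates.

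**Step 5: completers per arm.** Let p be the progression rate and d an assumed share of the remaining patients who stop early for other reasons. The protocol gives no value for d, so a range is shown. Control dosing is taken here to stop at month 24, purely to allow the calculation.

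Completers = 35 × (1 − p) × (1 − d)

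| Assumed d | Control (p = 0.42) | Abatacept (p = 0.11) | Difference |
|---|---|---|---|
| 0 | 35 × 0.58 = 20.3 (58%) | 35 × 0.89 = 31.2 (89%) | 31 points |
| 10% | 18.3 (52%) | 28.0 (80%) | 28 points |
| 20% | 16.2 (46%) | 24.9 (71%) | 25 points |

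These are patients with no scheduled contact after treatment ends, if every early stopper is seen again. Under that reading, at d = 0, at most 35 × 0.42 = 14.7 control and 35 × 0.11 = 3.9 abatacept patients have a later visit. The true numbers with a later visit are lower, because the 42% and 11% are cumulative two-year rates. They include progression first recorded at visit 10, after which nothing is scheduled. The d = 0 completer counts are therefore lower bounds on the patients without a later contact.

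**The case against.** A reader might infer that the window is simply unobserved in completers. The documents do not support that. Section 10 accepts spontaneous reports alongside elicited ones, asks for follow-up of events still present when treatment ends, and requires serious events to be reported through the 30 days. Serious events after that are to be reported if believed related to study drug or a protocol procedure. The gap is the absence of a scheduled contact, and it matters least for serious events. This part of the objection stands, although following up existing events does not find new ones, and after visit 10 nothing is scheduled at which to ask.

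A reader might also infer that the safety comparison between arms is biased. That goes further than the protocol allows, for four reasons:

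- Later visits for progressors take place only where possible, and no attendance rate is given.
- Stops for intolerance, toxicity or intercurrent illness (section 7.4) also create post-dose windows, and their split by arm is unknown.
- The control arm's dosing end is stated in two incompatible ways.
- The counts above are of patients without a contact, not of missed events. No post-dose event rate is given. Progressors are then treated at their physician's discretion, so their post-dose events are not directly comparable with those of completers.

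Unequal coverage by arm is therefore a possibility that follows from the planning rates under stated conditions. It is not an established bias.

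**Conclusion.** The contradiction between sections 8 and 10 is real: the visit schedule as written cannot deliver the post-dose collection that section 10 requires. For abatacept completers, about 16 to 30 of the 30 days rest on spontaneous reporting.

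Coverage could differ by arm by about 25 to 31 percentage points. That range assumes the planning rates hold, other early stopping is between 0 and 20% and equal in the arms, early stoppers attend later visits, and control dosing is taken to end at month 24. The direction of any undercount would be towards fewer recorded events on abatacept, but its size cannot be derived.

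The point is minor. It affects only the completeness of safety data, in about 4% of a completer's observation, and leaves the primary endpoint, sample size, power and alpha unchanged. The abatacept gap exists however the hydroxychloroquine duration is resolved.

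**What to change.** - Add one column to the schedule in section 8.8: a telephone safety contact at least 30 days after the last dose, with the adverse event row ticked. It should apply to every patient in both arms, completers and early stoppers alike.
- Reconcile the two statements of the hydroxychloroquine treatment period in sections 5.2 and 6.3, so that the window has a defined start in that arm.
- State in section 8.9 whether this call counts as the last visit for the end-of-study definition.

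The cost is at most 70 calls and one eCRF page. For a completer whose last dose is at month 24, the last data point moves to about month 25, which fits within the six months already planned after the last visit. How adverse events are then tabulated can be left to the SAP.
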